### 9.2. STATISTICAL METHODS

A detailed study statistical analytical plan for the final analysis, that will supersede the study protocol, will be drawn up during the course of the study before the unblinding of data at database lock.

#### 9.2.1. Trial profile and flowchart

A trial profile will be developed and presented as a flow chart following CONSORT guidelines, consisting of the number of participants screened, eligible, enrolled, randomized, and followed to 6 months post-discharge, number contributing to primary efficacy outcomes. It will also include the number of participants who withdrew or were lost to follow-up.

#### 9.2.2. Baseline characteristics

Descriptive statistics of baseline characteristics, overall and by treatment group will be provided in a table consisting of parameters collected prior to randomisation. No statistical comparisons

will be made between the groups, but any differences between groups at baseline which are also associated with the outcome variable will be taken into account in subsequent analysis.

### *9.2.3. Analysis Populations*

#### *9.2.3.1. Screening failures*

If a subject gives informed consent and is provided with a study ID, but then is lost from follow up, dies or withdraws before randomisation at 2 weeks from enrolment or does not fulfil the randomisation eligibility criteria, they will be classified as a randomisation screening failure and excluded from the ITT and the ATP analysis, but they contribute to a separate analysis of the risk and determinants of the different outcomes in the first 2 weeks since enrolment prior to randomisation.

#### *9.2.3.2. Intention to treat population*

The Intention-to-treat population is defined as all randomized subjects with a valid informed consent.

#### *9.2.3.3. Per protocol population*

The per-protocol population is a subset of the ITT population. Subjects with major protocol deviations will be excluded from PP population. Major protocol deviations will be defined in the Statistical Analysis Plan (SAP)

#### *9.2.3.4. Safety population*

All children who were randomized, received the first dose of study intervention and were followed up; i.e. provided information on potential adverse events.

### *9.2.4. Missing Data*

Every effort will be made to minimise the amount of missing data in the trial. Whenever possible, information on the reason for missing data will be obtained. No adjustments will be made for missing outcome data, but missing data may be imputed for co-variables.

### *9.2.5. Assessment of efficacy*

#### *9.2.5.1. Primary analysis*

Primary analysis will be by intention to treat, and include all primary endpoint events to capture the potential effect of PMC on reducing first and repeat events. The associated statistical null hypothesis is that there is no difference between the treatment groups in the distribution of the incidence rate of the primary endpoint, and the alternative hypothesis is that there is a difference between treatment groups.

The follow-up time will be measured as the time in days from the date of randomisation to the end of follow-up, death or drop-out. The incidence rate will be calculated per arm and the rate ratio (RR, PMC to placebo) and 95% confidence intervals (CI) estimated using Poisson regression models, stratified by country, with treatment (as randomized) as the only co-variate. The results will be expressed as the relative rate reduction (RRR) (95% CI) calculated as 100 multiplied by (1–RR).

In addition to the final analysis, the primary statistical hypothesis will be tested in an interim analysis when approximately half of patients are recruited as described in more detail in section 9.5.1.2, page 49.

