#### 8.8.1.2. Original sample size estimation

Sample size calculations were conducted using EAST (v6.2) Software. The total sample size will be 2212 children (1106 per arm) across both countries pooled. A sample size of 1858 is required to allow detection of a 30% reduction in the mean incidence rate (incidence density) of the composite primary outcome (death or all-cause readmission) from 469 per 1000 child years (216 events per 1000 children during the 24 weeks from randomization at 2 weeks to the end of follow-up at 26 weeks) in the control arm to 328 per 1000 child years (151 per 1000 children over 24 weeks) in the intervention arm (power 90%,  $\alpha=0.05$ ). A single child can have multiple (repeated) primary events. 1865 children are required to allow for 1 interim analysis using the Lan-DeMets spending function with O'Brien-Fleming type boundaries to preserve the overall two-sided type I error rate for efficacy (see 9.5.1.2, page 49). To allow for 15.7% loss to follow-up a total of 2212 children will be conducted.

The impact estimate of 30% is based on the previous trial in Malawi where the protective efficacy (PE) with monthly AL was 30% (and 31% for death or admission for malaria or anaemia). The incidence rate of 469 per 1000 child years is the average incidence rate observed during the 2-26 weeks post-discharge period in the control arm in the previous trial in Malawi (536 per 1000 child years) and the rate in western Kenya in 2013 (402 per 1000 child years). The estimated rate of loss to follow of 15.7% is conservative and three times the rate observed in our previous studies that involved 6 months follow-up of children admitted for severe malaria or severe anaemia: this was 7.4% in the earlier IPTpd/PMC trial in Malawi across 4 hospitals, and 3.5% and 5.0% in two previous observational studies in Uganda. However the study will involve a total of 7 hospitals, only 3 of which are experienced research hospitals. We have therefore allowed for 15.7% loss to follow-up, which is the average of 10% in the 3 experienced sites and 20% in the remaining 4 sites.

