##### *Clinical modifiers*

4. Syndrome on admission: non-malaria severe anaemia vs severe malaria anaemia. PMC is hypothesized to be more effective in children with severe malaria anaemia on enrolment as they represent a selected subgroup that is more exposed to malaria for environmental, behavioural or host-genetic reasons.
5. HIV status: HIV-infected vs HIV-uninfected. PMC is hypothesized to be more effective in HIV uninfected children as HIV-infected children may have high rates of readmissions due to other causes and may benefit from antimalarial prophylactic properties of daily cotrimoxazole.
6. Hb on randomization: Terciles. PMC is hypothesized to be more effective in children with the lowest Hb as they may be at highest risk of rebound severe anaemia without an intervention.
7. Previous hospital admittance: lowest 50% vs highest 50%. PMC is hypothesized to be more effective in children with a history of previous admissions as they represent a selected subgroup at highest risk of severe anaemia or malaria for environmental, behavioural or host-genetic reasons.

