#### *9.2.5.3. Sensitivity analysis*

A number of sensitivity analyses will be conducted to assess the robustness of the primary endpoint analysis. These include un-stratified Poisson regression models, analysis of the per-protocol subject population, and covariate adjusted analysis. Other regression methods including negative binomial regression and models for recurrent event time data will also be explored. Additional post-hoc analyses may also be conducted if deemed necessary. In addition, the results of the statistical models with and without imputation for missing values for co-variables values will be compared. Covariates for co-variate adjusted analysis and subgroup analysis, and alternative statistical models, which will be specified in the statistical analysis plan (SAP).

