## 9.8. ECONOMIC EVALUATION SUB-STUDY

The economic evaluation will provide information about incremental costs, incremental health benefits and cost-effectiveness of PMC compared to the current standard of care in Kenya and Uganda. The overall aims are to inform decision makers whether PMC as implemented in this trial is likely to be cost-effective if routinely implemented.

A novel decision-model (Figure 3) will be developed to capture aspects relating both to protective efficacy and to country specific implementation characteristics including different implementation costs. Since recurrent events are common, and since previous health events are risk factors for new events, a micro-simulation model is adequate to capture costs and health outcomes. The influence of single parameters will be analysed with one-way sensitivity analyses, while overall decision uncertainties will be estimated utilising probabilistic sensitivity analysis. Incremental costs will be calculated per case averted of severe anaemic malaria, per death averted and per disability adjusted life year (DALY) averted. Treatment efficacy will be based on the results of the proposed trial in Kenya and Uganda and on the pooled results from this trial and the previous trial in Malawi. DALYs will be calculated using standard assumptions from the recent Global Burden of Disease Study.

Figure 3 Micro-simulation model (M)

[figure not shown]

The interventions will be costed prospectively alongside the trial from the perspectives of both the health care provider and the patients/families. Costs will be calculated from a societal perspective, but results will be presented disaggregated for the health care provider and the patients/families. We will use an ingredients approach, in which resources in separate processes are identified, quantified and valued.

The economic evaluation requires collection of some data in addition to the main trial data. The families of the affected children face cost related to receiving the PMC treatment (intervention costs), and in addition they are subject to costs related to the primary disease, readmissions or

death (disease costs). Likewise, the health care providers need resources to provide the intervention, which in turn will affect future cases of disease.

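### The primary analysis counts repeat events per child but names no robust variance or dispersion term, so a model-based Poisson interval is likely to be too narrow, by an amount the protocol does not determine

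*Protocol*

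**What the plan says.** Section 9.2.5.1 of the protocol says the primary analysis will "include all primary endpoint events to capture the potential effect of PMC on reducing first and repeat events". Time at risk does not stop at a first admission: "The follow-up time will be measured as the time in days from the date of randomisation to the end of follow-up, death or drop-out". The rate ratio and 95% CI come from "Poisson regression models, stratified by country, with treatment (as randomized) as the only co-variate", and section 3.2 repeats this model. Section 8.8.1.2 confirms that "A single child can have multiple (repeated) primary events".

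Three other places bear on whether those counts behave as Poisson counts.

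- Section 9.8, explaining the economic model: "Since recurrent events are common, and since previous health events are risk factors for new events".
- Section 9.2.5.2, on children with previous admissions: "they represent a selected subgroup at highest risk of severe anaemia or malaria".
- Section 9.2.5.3, among the sensitivity analyses: "Other regression methods including negative binomial regression and models for recurrent event time data will also be explored".

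The revised sample size (section 8.8.1.1) is 520 per arm. It uses a test of the ratio of two Poisson rates and mentions no overdispersion. Section 9.2 says a later SAP will take precedence over the protocol; that SAP was not available.

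**The concern.** The usual standard error from a Poisson model is correct only if the variance of the per-child count equals its mean. That requires no dependence between events in the same child and no difference in risk between children beyond what the model contains, which here is country and arm. The protocol describes the opposite. Earlier events predict later ones. Risk also varies with admission history, with environmental, behavioural, nutritional and genetic factors (section 4.1) and with protective polymorphisms (section 8.2.6). Hospitals within one country range from moderate to intense transmission (section 8.3).

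If the variance exceeds the mean and the model-based standard error is used, the primary interval is too short and the primary p-value too small. This is the confirmatory test of a trial meant to inform WHO policy (section 7.1). Increasing the sample size does not cure it.

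**Working it through.** **Inputs** (section 8.8.1.1): control rate 1.152 and intervention rate 0.864 per child-year over 24 weeks, 520 per arm, 10% loss, 80% power, α = 0.05. I take α as two-sided, as section 8.8.1.2 does for the original design. The variance-to-mean ratio φ is my assumption, because the protocol gives none.

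**The plan's own figure.** Events per child over 24/52 year are 1.152 × 24/52 = 0.5317 and 0.864 × 24/52 = 0.3988. With ln(0.75) = −0.2877:

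n per arm = (1.960 + 0.842)² × (1/0.5317 + 1/0.3988) / 0.2877² ≈ 416 before loss, and 416/0.90 ≈ 462 after 10% loss.

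The stated 520 is not reproduced (416/0.80 = 520). That is a separate matter. Here it means only that 520 per arm with 10% loss, or 468 evaluable, leaves some spare power. The original total of 1858 is reproduced closely (1845) by the same independent-Poisson, two-sided formula.

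**Effect on the test.** The true SE is the model-based SE × √φ, so actual two-sided type I error = 2 × [1 − Φ(1.96/√φ)].

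**Effect on valid power.** Expected events are 468 × 0.5317 ≈ 249 and 468 × 0.3988 ≈ 187. The model-based SE of the log rate ratio is √(1/249 + 1/187) ≈ 0.0968. Power = Φ(0.2877/(0.0968√φ) − 1.96).

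| Assumed φ | True SE ÷ model SE | Two-sided type I error, model-based | Half of it, favouring the drug (nominal 2.5%) | Power, valid test |
|---|---|---|---|---|
| 1.0 | 1.00 | 5.0% | 2.5% | 84% |
| 1.1 | 1.05 | 6.2% | 3.1% | 81% |
| 1.25 | 1.12 | 8.0% | 4.0% | 76% |
| 1.5 | 1.22 | 11.0% | 5.5% | 68% |

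Power reaches 80% at φ = 468/416.2 ≈ 1.12.

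**Simulation.** With gamma-distributed child risk, 468 per arm, mean 0.53 events per child, no treatment effect and 40,000 trials per setting, model-based Poisson rejected in 6.4%, 7.9% and 11.2% of trials at φ = 1.11, 1.27 and 1.53. A per-child robust variance rejected in 4.9–5.2%. The simulation had no country strata and no terminal death.

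**What the protocol suggests about φ.**

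- *Polymorphisms.* Section 8.2.6 puts them above 20%, with 70–90% protection against severe malaria. Suppose 20% of children have 70–90% fewer events and the pooled mean is 0.46. At 70%, the squared coefficient of variation of risk is 0.2 × 0.8 × 0.7² / 0.86² = 0.106, so φ = 1 + 0.106 × 0.46 ≈ 1.05. At 90% it is 0.2 × 0.8 × 0.9² / 0.82² = 0.193, so φ ≈ 1.09. Not all events are malaria, so this overstates that one factor, but it is only one of several.
- *Western Kenya.* A rate of 0.402 per child-year (section 8.8.1.2) gives 0.201 events in 6 months. A pure Poisson count predicts 1 − e^(−0.201) = 18.2% of children with an event, against 17.9% reported (section 4.1). A gamma-Poisson fit gives a dispersion parameter of about 0.19, or φ ≈ 1 + 0.19 × 0.46 ≈ 1.09.
- *Uganda.* Pairing the reported 36.5% with the assumed control mean of 0.53 gives φ ≈ 1.35.

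The last two pairings may mix cohorts and definitions, so neither estimates φ for this trial.

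**The case against.** The strongest reply is that section 9.2.5.1 names Poisson regression but not how its standard error is obtained. A sandwich variance is compatible with that text, the choice is often left to an SAP, and section 9.2 says the SAP prevails. This stands to the extent that the protocol does not prescribe a model-based standard error. It does not dispose of the point. The section sets out the primary model, its stratification and its covariates, and places every method that deals with overdispersion among sensitivity analyses to be explored. Followed as written, it gives the model-based interval. Sensitivity analyses would make a discrepancy visible but would not protect the primary p-value.

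Four further replies have force. Section 9.8 justifies the structure of an economic model and does not measure dispersion. Stratifying by country removes between-country differences. Known sickle cell disease is excluded. Death happens once and ends follow-up, which pulls slightly against overdispersion. These may make φ modest, but they do not remove the within-country and within-child sources.

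A reader might infer that type I error is shown to be 10% or more, or that the trial is underpowered. The documents support neither. The higher error rates need φ near 1.5, which nothing in the protocol establishes, and the Kenyan comparison points lower. Power stays at or above the stated 80% until φ passes about 1.12.

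**Conclusion.** The concern holds in direction and is conditional in size. The protocol counts all events, expects recurrences to depend on earlier ones, and names no allowance for this in the primary interval. If the standard error is model-based and φ exceeds 1, the interval is too narrow by √φ. True two-sided type I error is then about 6%, 8% and 11% at φ of 1.1, 1.25 and 1.5, with roughly half of those rejections favouring the drug. Valid power at 520 per arm with 10% loss is 84%, 81%, 76% and 68% at φ of 1, 1.1, 1.25 and 1.5. These figures assume a two-sided 5% test, the planning rates, and a φ that the protocol does not supply. It should be settled before unblinding because it concerns the confirmatory test and the remedy costs little.

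**What to change.** State in section 9.2.5.1, and in the SAP, that the primary CI and p-value come from one of two models, named in advance:

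- the country-stratified Poisson rate model with log person-time as offset and a robust (sandwich) variance at child level; or
- negative binomial regression with the same stratification and offset.

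Keep the model-based Poisson fit as a sensitivity analysis. Estimate the dispersion from the blinded pooled event counts used for the sample size re-estimation, which needs no unblinding, and give power over a range around that estimate.

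The cost is wording and a short blinded calculation, with no new data. If φ is near 1 the interval hardly changes. If it is larger, the interval widens (for a rate ratio of 0.75, from 0.62–0.91 to about 0.61–0.93 at φ = 1.25) and the stated power may have to come down.

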**Data Analysis:** Primary analysis will be by intention to treat. Incidence rates will be calculated and rate ratios estimated using Poisson regression, stratified by country, with treatment (as randomised) as the only co-variate. To assess how long any initial beneficial effect of PMC is sustained, the observation time will also be divided into a) PMC period (2-14 weeks); and b) Extended follow-up period (15-26 weeks post-discharge).

**Partners institutions:** University of Bergen; University of Malawi; Makerere University; KEMRI-CDC, Kenya; University of Indiana; Liverpool School of Tropical Medicine; London School of Hygiene & Tropical Medicine; Imperial College London; University of Amsterdam; US Centers for Disease Control and Prevention, University of North Carolina, and University of Massachusetts.

Table 1: Study treatment and phases

| 
AL      PMC1      PMC2      PMC3
 
0      2      6      10      14      26
 
Enrolment      Randomisation
 
Time since enrolment (weeks)
 |                                                     |                                    |                                        |
|----------------------------------------------------------------------------------------------------------------------------------------------------------------|-----------------------------------------------------|------------------------------------|----------------------------------------|
| Period                                                                                                                                                         | Pre-PMC                                             | PMC                                | Post-PMC(extended follow-up)           |
| Trial intervention                                                                                                                                             | AL near discharge, both arms                        | Three DP courses as PMC or placebo | No intervention                        |
| Rescue Rx acute malaria                                                                                                                                        | Oral QN, 7 days                                     | AL, 3 days                         | AL, 3 days                             |

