## 8. DESIGN AND METHODOLOGY

### 8.1. OVERVIEW STUDY DESIGN

This will be a multi-centre, parallel group, two-arm, placebo-controlled, individually randomized, superiority trial with 1:1 allocation ratio comparing the safety and efficacy of three courses of monthly PMC-DP or placebo post-discharge provided in addition to the standard single 3-day treatment course with artemether-lumefantrine provided as part of standard in-hospital care. Randomisation to PMC-DP or placebo will occur at 2 weeks after enrolment, and PMC-DP treatments will be administered at 2, 6 and 10 weeks. The primary outcome will be a composite of death or all-cause readmission between 2-26 weeks after enrolment. The study will be conducted in Uganda and Kenya, using randomisation stratified by age and study centre. The study will include a total of 1040 children (520 per study arm) less than 5 years of age who have been admitted for all-cause severe anaemia and have successfully completed the standard in-hospital treatment.

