## 8.10. ASSIGNMENT OF INTERVENTIONS AND BLINDING

### 8.10.1. Allocation

#### 8.10.1.1. Allocation sequence generation

Eligible children will be randomly assigned to either PMC or placebo group with a 1:1 allocation as per a computer generated randomisation schedule stratified by age group and site using permuted blocks of random sizes. The length of each block will be randomised and will not be disclosed to ensure blinding is fully maintained.

The randomisation schedule will be drawn-up in advance by the study statistician. Recruitment will be 'competitive' between the sites within a country (i.e. the number of subjects recruited at each site may differ depending on the respective rates of admission). To allow for this, 600 individual randomisation envelopes will be prepared for each site to ensure equal distribution across study arms within each site.

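### The primary model is stratified by country only, although randomisation is stratified by site and age group: negligible for a plain Poisson interval, mildly conservative once the variance allows for repeat events

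*Protocol*

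**What the plan says.** Section 8.10.1.1 describes a "randomisation schedule stratified by age group and site using permuted blocks of random sizes". Section 8.1 agrees: "using randomisation stratified by age and study centre". Country is not named as a stratum.

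Section 9.2.5.1 fixes the primary analysis as Poisson regression "stratified by country, with treatment (as randomized) as the only co-variate", and the summary in 3.2 repeats this ("stratified by country, with treatment (as randomised) as the only co-variate"). The outcome is a count that may exceed one per child, since the analysis is to "include all primary endpoint events to capture the potential effect of PMC on reducing first and repeat events". Neither section names a robust or overdispersion-scaled variance.

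Site and age group appear in 9.2.5.2 as subgroup factors. The sensitivity analyses in 9.2.5.3 are described as follows: "These include un-stratified Poisson regression models, analysis of the per-protocol subject population, and covariate adjusted analysis". Negative binomial and recurrent-event models are to be explored there as well, and the covariates for adjusted analysis are left to the SAP.

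Section 9.2.2 says of baseline tables that "any differences between groups at baseline which are also associated with the outcome variable will be taken into account in subsequent analysis".

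**The concern.** A primary analysis normally conditions on the factors used to restrict randomisation. Here one factor (age group) is absent and the other (site) survives only as country. Country does not stand in for site: section 8.3 lists places of differing transmission within each country, for example Siaya (high) and Kisumu (moderate) in Kenya, and Tororo (intense) and Jinja (moderate, seasonal) in Uganda.

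This is not a detail left to the SAP, because the protocol fixes the primary model itself and gives no reason for the coarser stratification. At stake are the width of the reported interval and some power, if rates differ by site within country or by age. A smaller matter is 9.2.2, which describes choosing covariates from observed imbalance and association with outcome, while 9.2.5.3 expects a list set out in the SAP.

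**Working it through.** **Planning figures (section 8.8.1.1).** 520 per arm with 10% loss leaves 468 followed. Expected events per child over 24 weeks are 0.530 (control) and 0.398 (intervention). Two-sided α = 0.05 is assumed, because the revised calculation does not state sidedness.

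The stated total of 1040 does not reproduce exactly. (1.960 + 0.842)² × (1/0.530 + 1/0.3975) / (ln 0.75)² = 417.5 per arm, and 417.5/0.9 = 463.9, or about 928 in total. With 468 followed per arm, power is 84.3%. The difference is in the safe direction and does not bear on this point.

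**Plain Poisson standard error.** Events are d0 = 468 × 0.530 = 248 and d1 = 468 × 0.398 = 186. Without strata, SE(log RR) = √(1/248 + 1/186) = √0.00940 = 0.097.

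With strata s, the information on log RR is Σ d0s·d1s/(d0s + d1s). If blocking makes d1s/d0s about the same in every stratum, this sum equals d0·d1/(d0 + d1), so the SE is again 0.097. Adding balanced strata therefore gains nothing under the model-based SE.

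**Robust standard error with strata left out.** Let V be the squared coefficient of variation of rates across the omitted strata. Each arm's residual variation then includes it, and the variance is about 1/d0 + 1/d1 + 2V/468. For illustration, assume an even age split and all site variation within country:

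- Site SD 0.3 on the log rate, age rate ratio 1.5: V = e^0.09 × (1 + 0.25²/1.25²) − 1 = 0.138. SE = √(0.00940 + 0.00059) = 0.100.
- Site SD 0.5, age rate ratio 2: V = e^0.25 × (1 + 0.5²/1.5²) − 1 = 0.427. SE = √(0.00940 + 0.00182) = 0.106.

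The randomisation has already removed this component from the estimate's true variation, so including it makes the interval too wide.

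**Simulation.** 936 children, RR 0.75, permuted blocks within site by age group, robust SE. Site SD, age rate ratio and child-level frailty variance are all assumed. There were 600 trials per setting with 12 sites and 1000 with 8 sites.

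| Sites | Site SD / age RR / frailty | SE, country only | SE, site + age | Ratio | Power, country vs site + age |
|---|---|---|---|---|---|
| 12 | 0.2 / 1.3 / 0 | 0.0980 | 0.0963 | 1.02 | 85.0 vs 86.0% |
| 12 | 0.4 / 1.5 / 0 | 0.1010 | 0.0965 | 1.05 | 81.7 vs 84.5% |
| 12 | 0.6 / 2.0 / 0 | 0.1065 | 0.0963 | 1.11 | 79.0 vs 83.8% |
| 8 | 0.3 / 1.5 / 0 | 0.0998 | 0.0966 | 1.03 | 82.9 vs 84.0% |
| 8 | 0.5 / 2.0 / 0 | 0.1049 | 0.0967 | 1.08 | 77.9 vs 82.2% |
| 8 | 0.3 / 1.5 / 0.5 | 0.1110 | 0.1080 | 1.03 | 77.0 vs 79.4% |
| 8 | 0.5 / 2.0 / 0.5 | 0.1177 | 0.1104 | 1.07 | 70.2 vs 74.0% |

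With no site or age effect, the 8-site SEs nearly coincide (0.0970 vs 0.0966).

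Further results from the 8-site runs:

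- *The estimate itself.* Its sampling SD is the same under both models: 0.0968 vs 0.0968, 0.1024 vs 0.1019, 0.1042 vs 0.1042 and 0.1100 vs 0.1100, in the order of the 8-site rows.
- *Model-based SE, no frailty.* Power is 83.7 vs 83.8% and 82.5 vs 82.1%. The covariates make no difference.
- *Type I error, robust SE.* Country-only rejects 3.6% and site + age 5.4% (site SD 0.5, age RR 2, no frailty). With frailty variance 0.5 the figures are 3.4 vs 3.6% and 4.6 vs 5.6%.
- *Type I error, model-based SE with frailty variance 0.5.* About 7% and 10%, whichever covariates are used.

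Simulation error is about 1.2 points for power and 0.7–1.0 points for type I error.

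**The case against.** The strongest reply is that nothing is lost under the model as written. Section 9.2.5.1 says Poisson regression and no more. Under its usual SE the two models agree, and the stratified allocation has already done its work in the estimate. That stands. A reader might infer that the country-only model throws away precision built into the design; the equal sampling SDs show that it does not. What can be too wide is the reported interval, and only under a robust or scaled variance.

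The reply does not dispose of the point, because the plain SE is not safe for this outcome: with frailty variance 0.5 it rejects 7–10% under the null. Once that is repaired, the cost of omitting the strata appears. The unnamed variance is the larger of the two matters.

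A second reply is that the heterogeneity is assumed. This also stands. The protocol gives no site-specific rates within the trial's countries and no age-specific rates. Its contrast between settings (17.9% in western Kenya and 36.5% in Uganda, section 4.1) is one that country already carries. Nor does naming age as an effect modifier in 9.2.5.2 show that age predicts the event rate. The better ground for including age is that the design stratifies on it.

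A third reply is that pooling small sites could become a choice made on the data. That is a fair warning, met by fixing the rule in advance.

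On 9.2.2, a reader might infer that the primary result is open to selective adjustment. It is not: 9.2.5.1 allows no covariate but treatment, and 9.2 requires the SAP before unblinding.

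**Conclusion.** The mismatch is real and unexplained, and it should be corrected, but its effect is modest. With the model-based Poisson SE, precision is unchanged. With a robust SE, the country-only interval is conservative: about 2–11% wider than the interval from site plus age group, with about 1–5 points less power. The upper figures need a site SD of 0.6 and an age rate ratio of 2; the lower figures (2%, one point) come from a site SD of 0.2 and an age rate ratio of 1.3. These effects are assumptions, so the range is an illustration and not a forecast. Only the robust form was simulated; an overdispersion-scaled variance should behave alike, because it too puts between-stratum variation into the error. The documents do not support a claim of bias or of inflated type I error from omitting the strata. Section 9.2.2 is loosely worded, which is a minor point.

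**What to change.** 1. In 9.2.5.1 and the summary in 3.2, specify Poisson regression with treatment plus the randomisation strata, site and age group. State a rule for pooling small sites within country, with its threshold fixed before unblinding.
2. In the same place, name a variance that allows for repeat events within a child (robust, or scaled for overdispersion).
3. Keep the country-only model as a sensitivity analysis in 9.2.5.3. If the sponsor prefers it as primary, give the reason.
4. Reword 9.2.2 so that covariates for adjusted sensitivity analyses come only from the list pre-specified under 9.2.5.3, not from observed imbalance and association with outcome.

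The cost is wording only. Site and age group are known for every randomised child, and neither the sample size nor data collection changes.
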